## Abstract

**Background:**

Patients with an advanced incurable disease are often hospitalised for some time during the last phase of life. Care in hospitals is generally focussed at curing disease and prolonging life and may therefore not in all cases adequately address the needs of such patients. We present the COMPASS study, a study on the effe***c***ts and c***o***sts of consultation tea***m***s for ***pa***lliative care in ho***s***pital***s***.

This observational study aims to investigate the use, effects and costs of PCT consultation services for hospitalized patients with incurable cancer in the Netherlands.

**Methods/design:**

The study consists of 3 parts:

1. A questionnaire, interviews and a focus group discussion to investigate the characteristics of PCT consultation in 12 hospitals. PCTs will register their activities to calculate the costs of PCT consultation.

2. Cancer patients for whom the attending physician would not be surprised that they would die within 12 month will be included in a medical file search in three hospitals. Medical records will be investigated to compare care, treatment and hospital costs between patients with and patients without PCT consultation.

3. In the other nine hospitals, we will perform a longitudinal study, and compare quality of life between 100 patients for whom a PCT was consulted with 200 patients without PCT consultation. Propensity score matching will be used to adjust for differences between both patient groups. Patients will be followed for three months after inclusion. Quality of life will be assessed with the Palliative Outcome Scale, the EuroQol-5d and the EORTC-QLQ-C15 PAL. Satisfaction with care in the hospital is measured with the IN-PATSAT32. The cost impact of PCT consultation will also be explored.

**Discussion:**

This is the first multicenter study on PCT consultation in the Netherlands. The study will give valuable insight in the process, effects and costs of PCT consultation in hospitals. It is anticipated that PCT consultation has a positive effect on patients’ quality of life and satisfaction with care and will lead to less hospital care costs.

## Background

Patients with an advanced incurable disease often spend some time in hospital during the last months of life [1]. When death is approaching for such patients, the goals of care need to be realigned. However, burdensome medical interventions are often prolonged until the end of life, without any beneficial effect [2–5]. As a result, end-of-life care in hospitals tends to involve high costs while failing to address patients’ needs and to provide them with a dignified death.

Palliative care is aimed at acknowledging patients’ impending death and at reconsidering goals of care [6]. It is an approach that improves the quality of life and their families facing the problems associated with life-threatening illness, through the prevention and relief of suffering by means of early identification and impeccable assessment and treatment of pain and other problems, physical, psychosocial and spiritual [7]. Palliative care is not only provided at the end of life, but also in earlier stages, sometimes alongside disease-directed interventions that are aimed at curing disease or prolonging life [8]. Basic palliative care, such as basic symptom management and supporting patients to align their treatment choices with their values and goals, should be delivered by any health professional attending patients in the last phase of life. Other, more complex forms of care, such as managing refractory symptoms or negotiating a difficult family meeting, may require involvement of specialized palliative care professionals [8].

### The effects of palliative care team consultation

Several studies have shown that the deployment of specialized palliative care teams (PCTs) in hospitals is associated with better outcomes for patients with advanced disease [9]. Their involvement was found to improve patients’ quality of life [10–12], their satisfaction with care [12, 13] and communication about goals of care, resulting in less diagnostic testing and less use of inappropriate technology and intensive care [14]. In a recent study Temel et al. found that patients with lung cancer receiving early palliative care had a better quality of life, received less aggressive treatment and had a longer survival compared to patients receiving usual care without palliative care involvement [15]. Consultation of palliative care services for patients with advanced incurable disease may also influence health care costs, through its focus on assessing patients’ goals of care and providing treatments that are concordant with these goals. Several studies have demonstrated significant cost savings as a result of palliative care involvement [13, 14, 16–18]. The largest group of patients who are referred to specialized palliative or end-of-life care services consists of patients with incurable cancer, in the Netherlands as well as in other countries [19, 20]. However, the provision of palliative care to patients with advanced cancer often remains suboptimal. Informational, emotional and physical needs are frequently unmet among patients with incurable disease [21–24]. Studies show that PCT consultation is only used for a minority of all patients with advanced disease, which suggests that this service is used sub-optimally [25]. This might be due to a lack of awareness of the availability and potential contribution of this service among regular health care professionals. Furthermore, it is known that PCTs are often consulted late in the disease trajectory [26]. There may also be barriers to consultation, such as the lack of referral criteria, and the view that the involvement of palliative care is a signal that the primary health care professionals have given up all hope for a patient [27–29].

### Palliative care team consultation in hospitals in the Netherlands

The Netherlands has a nationwide system of palliative care consultation services, that is predominantly used by general practitioners for patients staying at home [30–32]. More recently, hospitals have started establishing PCT consultation services. An inventory of the Comprehensive Cancer Centre Netherlands in 2013 showed that at least 45 hospitals in the Netherlands, out of a total of 92, were in different stages of implementing such consultation services [33]. Most hospital-based specialist PCTs can be consulted by physicians or nurses working in the hospital. Upon their involvement, PCTs typically provide a detailed holistic assessment of the patients’ and family´s situation. They assess patients’ symptoms and their physical, emotional, social and spiritual problems, prioritize these and propose a care plan to address them. The extent to which PCTs provide care themselves or only advise the primary caregivers varies. Most PCTs consist of professionals from different specialties, such as oncologists, neurologists, anaesthesiologists, nurses, and psychosocial and spiritual caregivers. The structure and activities of PCTs in hospitals vary. Some PCTs are strongly embedded in the hospital and supported by their hospital boards, whereas others are not. Some teams are involved in education within or outside the hospital.

### Objectives

Evidence on the effects of PCT consultation in hospitals on patient outcomes and health care costs mainly comes from studies from the United States. It is unclear to what extent these results can be generalized to other countries with different health care systems and cultures, such as the Netherlands. We will therefore perform an observational study to investigate the use, effects and costs of PCT consultation services for hospitalized patients with incurable cancer in the Netherlands. We willassess the characteristics of PCT consultation services in different hospitals,study whether PCT consultation for patients with incurable cancer has an effect on in-hospital medical care,explore whether PCT consultation for patients with incurable cancer has beneficial effects on patients’ quality of life and satisfaction with care andexplore whether PCT consultation reduces costs of care and might be a cost-effective intervention.

## Methods

We will collect data in three substudies.

### Characteristics of PCT consultation in Dutch hospitals

We will use a structured questionnaire to study structure and process characteristics of PCT consultation services in 12 hospitals in the Netherlands. All teams will be asked to fill out this questionnaire, which contains multiple choice and open questions regarding the disciplines that are represented in the PCT, the process of consultation and the way the teams monitor and improve the quality of their consultation. Further, all teams will be invited to participate in group discussions or individual interviews to explore differences between teams and PCT members’ experiences of barriers and facilitators of a successful consultation service.

### The effect of PCT consultation for patients with incurable cancer on medical care

In three hospitals, care and treatment as provided to patients with advanced incurable cancer for whom a PCT is consulted during their stay in the hospital will be compared with care and treatment as provided to comparable patients without PCT consultation. Inclusion criteria are that patients are 18 years or over and that the attending physician answers “no” to the question “Would you be surprised if this patient would die in the next year?”. We will check the medical files of all eligible patients to assess the use of diagnostic procedures, medication, chemotherapy and other medical interventions, and days spent in hospital, during 3 months after inclusion. The attending physician will be asked to provide information on the patient’s diagnosis, performance status, co morbidity and life expectancy, by filling out a short questionnaire. For those patients for whom a PCT is consulted, PCTs will be asked to fill out a questionnaire about the content of the consultation.

The use of medical care and the number of days spent in hospital will be compared between patients with PCT consultation and patients without PCT consultation, while taking into account differences in patients’ medical characteristics.

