### Economic evaluation

The economic evaluation of PCT consultation in hospitals will concern a period of three months after admittance of patients to the hospital.

Data from substudy 2 will be used to perform a cost-minimisation analysis including hospital costs. We will distinguish intramural medical costs (inpatient days, professional health caregivers’ activities, medical procedures). Real medical costs will be calculated by multiplying the volumes of health care use with the corresponding unit prices. Costs for inpatient days in hospitals will be estimated as real, basic costs per day using detailed hospital administrative information. We will make a distinction between the costs in general hospitals and university hospitals. The unit price of the PCTs will be determined with the micro-costing method [43], which is based on a detailed assessment of all resources used.

Data from substudy 3 will be used to perform an economic evaluation from a health care perspective. We will calculate total medical costs per patient, including intramural and extramural medical costs (home care, nursing home days, general practitioner activities). For the calculation of the intramural medical care costs and the unit price of PCTs we use the same methodology as for the cost-minimisation study. For the calculation of extramural medical costs, we will use charges as published in Dutch guidelines as a proxy of real costs [44]. The cost-effectiveness of PCT consultation will be assessed by calculating the incremental cost-effectiveness ratio (ICER), defined as the difference in costs of PCT consultation compared to usual care, divided by the average change in patients’ quality of life . The primary effect measure for the economic evaluation of PCT consultation is quality of life as measured by the EORTC QLQ-C15. Because of the short time horizon, costs and effects will not be discounted.

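### Substudy 2 forms the PCT group by an event during the stay but counts days and costs from the start, so longer stays alone produce an apparent excess in PCT patients

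*Protocol article*

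**What the plan says.** The Methods section on medical care (substudy 2) compares care given to "patients with advanced incurable cancer for whom a PCT is consulted during their stay in the hospital will be compared with care and treatment" of similar patients for whom no PCT was consulted. The outcomes are diagnostic procedures, medication, chemotherapy, other interventions and "days spent in hospital, during 3 months after inclusion". The section does not say when inclusion takes place. The statement that patients enter on arrival stands in the next section and concerns substudy 3.

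Under Economic evaluation, the cost period "will concern a period of three months after admittance of patients to the hospital". The same section adds: "Data from substudy 2 will be used to perform a cost-minimisation analysis including hospital costs". The cost components are "intramural medical costs (inpatient days, professional health caregivers’ activities, medical procedures").

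The substudy 2 comparison is to be made "while taking into account differences in patients’ medical characteristics". The Data analysis section adds a propensity model. Its covariates are demographic, diagnostic, prognostic and hospital variables. None is the number of days already spent in hospital or the time until consultation.

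**The concern.** To be consulted during a stay, a patient must still be alive and in hospital when the consultation happens. Someone discharged on day 2 has had two days in which to become a PCT patient; someone discharged on day 20 has had twenty. The no-PCT group therefore collects the short stays and the PCT group the long ones, whether or not consultation does anything.

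Hospital days are an outcome of substudy 2 and a component of its cost-minimisation analysis, so the selection acts directly on what is measured. Perfect balance at admission would not help, because the fault lies in when exposure is assigned and not in case mix. The article anticipates lower hospital costs with PCT consultation. This bias pushes the other way and could hide or shrink a real saving.

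**Working it through.** **The plan's own figures.** Substudy 2 has no sample-size or effect figure to reproduce. The article's one power statement (100 against 200 patients, effect size 0.4, 90% power) belongs to substudy 3. It reproduces at 0.904 and has no bearing here.

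**Assumptions (none is in the article).** One stay per patient, mean 8 days, gamma distributed with shape s = 1 (exponential), 2 or 4. One third of patients are consulted. A fraction f of the consultations occurs at admission, independently of stay; the rest occur at a constant daily rate. No deaths, no readmissions, zero effect of consultation.

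**Formulas.** Let q be the share consulted among patients not consulted at admission: q = (1/3 − f/3) / (1 − f/3).
- Mean stay without consultation: x = 8 × (1 − q)^(1/s).
- The overall mean is 8 and one third are consulted, so the mean stay with consultation is 24 − 2x.
- Spurious excess: (24 − 2x) − x = 24 − 3x.

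**Results in days, PCT against no PCT, with the excess in brackets.**

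| Consultations at admission | q | s = 1 | s = 2 | s = 4 |
|---|---|---|---|---|
| None (constant rate) | 1/3 | 13.3 vs 5.3 (8.0) | 10.9 vs 6.5 (4.4) | 9.5 vs 7.2 (2.3) |
| Half | 1/5 | 11.2 vs 6.4 (4.8) | 9.7 vs 7.2 (2.5) | 8.9 vs 7.6 (1.3) |
| 80% | 1/11 | 9.5 vs 7.3 (2.2) | 8.7 vs 7.6 (1.1) | 8.4 vs 7.8 (0.6) |

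Simulation of 2,000,000 stays per shape agrees with these values.

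**Readmissions.** A separate simulation used mean stays of 7 or 10 days, shapes 1 or 2, mean waits to consultation of 10, 20 or 40 days, and 0 or 0.5 readmissions on average, with days counted to day 90. Over the 24 combinations the excess was 3.6 to 9.95 days. Readmissions left the absolute excess almost unchanged and lowered the relative one. With mean stay 10 days, exponential, and mean wait 20 days, it went from 16.6 vs 6.7 days (+149%) to 21.5 vs 11.6 days (+85%).

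**Adjustment for prognosis.** Let 40% of patients have a poor prognosis, die earlier, and be consulted four times as fast. The crude excess falls to 5.8 days, yet it is 7.1 days within the poor stratum and 8.9 within the good one. Stratifying on prognosis does not remove it.

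**Aligning the clock.** On the same 24 data sets, days after consultation were compared with days from the same hospital day in patients still in hospital and not yet consulted. The differences were −0.5 to +0.4 days, with standard errors of 0.09 to 0.28. In the 8-day constant-rate setting they were within 0.02 day of zero.

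**Substudy 3, same 8-day constant-rate setting.** Taking actual stays of 3 days or more as a proxy for the expected-stay criterion, the excess for s = 1, 2, 4 is 6.0, 3.4 and 2.0 days against comparators from the same hospitals, and 3.3, 2.1 and 1.3 days against comparators from hospitals without a PCT.

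**The case against.** **The clock for days is not fully fixed.** Inclusion is undefined in substudy 2. If PCT patients were included at consultation, the result for days would change. This stands as a limit. But the text does not say so, comparators would still have no corresponding start, and the cost clock is set at admission in any case.

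**The size depends on when consultations happen.** This stands. If most occur at admission, little is left, so 2.3 days is not a lower bound.

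**A reader might infer that the study will report longer stay and higher cost with PCT.** The article does not support that. The direction derived here is that of one mechanism. Earlier death among PCT patients would cut their three-month days and cost, and the net sign is uncertain.

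**A reader might infer that the excess consists of days before the consultation being charged to the PCT.** Early days are counted in both groups. The bias comes from selecting longer stays.

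**A reader might carry the figures over to the substudy 3 ICER.** Three of its nine hospitals have no PCT, so group membership there cannot depend on stay, and an expected stay of at least 3 days is required. The bias remains but is smaller.

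**The article is condensed, and its cost aims are exploratory.** Landmark or time-varying methods could sit in an unseen analysis plan. However, the article itself states the grouping rule and both starting points, and following them gives a non-zero answer under no effect. The aim concerning in-hospital care is not worded as exploratory.

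**Conclusion.** The concern holds for the days, care and hospital costs of substudy 2. Classifying by a consultation during the stay while counting from the start biases the comparison towards more days and higher cost with PCT, and the stated baseline adjustments cannot correct this. The direction of this mechanism is general wherever consultation requires a continuing stay. Its size cannot be known from the article. Under a mean stay of 8 days with one third consulted, it is about 2.3 to 8.0 days at a constant consultation rate and about 0.6 to 2.2 days if 80% of consultations occur at admission. The net estimate may differ, because confounding can act in the opposite direction. Substudy 3 carries a smaller version of the same problem.

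**What to change.** For substudy 2:
- Define the moment of inclusion and record the date of each consultation.
- Match each patient consulted on hospital day k to patients in hospital, alive and not yet consulted on day k, who are similar on baseline characteristics and on resource use before day k.
- Count days, procedures and costs from day k in both groups.
- State a rule for comparators who are consulted later, for example censoring at consultation with weighting.
- Report totals from admission as descriptive only.

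For substudy 3, any change of clock must put costs and quality of life on the same time zero, since quality of life is measured on fixed days after admission. Otherwise, present it as a sensitivity analysis of the ICER.

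Cost: one extra date per consultation, which the questionnaire already completed by the PCT could carry, plus a more elaborate matched analysis. Stay and procedure data come from the files already being searched. The downside is some loss of comparators for late consultations.

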### The effect of PCT consultation for patients with incurable cancer on quality of life and the cost effectiveness of PCT consultation

In 9 hospitals we will study the effect of PCT consultation for in-hospital patients with incurable cancer on quality of life. In order to get a good overview of different types of hospitals, a university hospital, teaching and general hospitals will be included. In order to include sufficient comparable patients receiving usual care 3 hospitals without a PCT will be included.

Inclusion criteria are that patients are 18 years or over; that the attending physician answers “no” to the question “Would you be surprised if this patient would die in the next year?”; and that the patient is expected to stay in the hospital for at least 3 days. The latter criterium is added to enable an informed consent procedure. Patients will be included upon arrival in the hospital. Eligible patients will receive an information letter, and will be informed and asked to participate by an attending nurse. Patients who agree to participate will be followed during three months, regardless of where they stay. The attending physician will be asked to fill in a questionnaire to assess medical information such as diagnosis, performance status, co morbidity and life expectancy. Palliative care consultation teams are asked to fill a questionnaire about the content of the consultation. Patients will be asked to fill out a number of subsequent questionnaires. In these questionnaires, quality of life is assessed with the EORTC QLQ-C15 PAL [34]. We will also measure quality of life with the Palliative Outcome Scale [35] and the EuroQol-5D [36] , because of the lack of consensus on the most appropriate quality of life instrument for patients with incurable disease [37]. Secondary measures are symptom scores for pain, dyspnoea and anxiety (EORTC QLQ-C15); patient satisfaction with care, using the INPATSAT 32 questionnaire [38, 39]. Quality of life will be assessed longitudinally at six moments in time: at day 4, 7, 14, 30, 60 and 90 after admission to the hospital; satisfaction with care will be assessed at day 14 after admission.

We aim to include 100 patients for whom a PCT was consulted and compare them with at least 200 patients receiving usual care. With such a sample size we will be able to detect a difference in quality of life as measured by the EORTC QLQ-C15 PAL at day 14 of 0.4 in standard deviation units (Cohen’s D = effect size) with alpha of 0.05 (2-sided) and power of 90 %.

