### Data analysis

Due to the observational design of the study it is likely that there is an imbalance of prognostic factors between patients who are and patients who are not receiving PCT consultation. As a consequence the estimated effects of PCT consultation can be biased. We will adjust for imbalance in the statistical analysis by using propensity scores [40–42].

We will develop a propensity score model to assess the probability that a patient would have been offered PCT consultation. Patient characteristics to be included in this model are age, sex, marital status, primary diagnosis, reason for hospitalization (e.g. treatment of complex symptoms, palliative chemotherapy, treatment of complications), life expectancy, functional status, attending physician specialty, comorbidity, and hospital of admission [14, 16]. The logit of the propensity score will be used to match each patient receiving PCT consultation with one or more usual care patients.

Quality of life scores at different time points will be compared between the PCT and care as usual groups with repeated measurement analysis. A model will be fitted that includes matched-pairs, time, treatment group, the baseline score, and interaction between time and treatment group.

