### Threats and opportunities

The threats to the successful conduct of this study relate mainly to the inclusion of patients. Nurses may be reluctant to ask patients for informed consent as participation in research may impose undue burden on patients and caregivers [47]. However, studies have found that many patients with advanced illnesses actually appreciate to participate in research [47]. Furthermore, it is known that PCTs are often consulted relatively late in the disease trajectory [27, 48], which means patients may not be able to participate by filling in questionnaires. Furthermore, some patients will be lost to follow up, which is inherent to the study population.

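### Substudy 3 times every outcome from admission but labels a patient PCT whenever the consultation occurs, so scores taken before the first consultation are analysed as PCT outcomes

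*Protocol article*

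**What the plan says.** All statements are in the protocol article and concern substudy 3.

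- **Entry** (Methods, quality of life and cost effectiveness): "Patients will be included upon arrival in the hospital".
- **Outcome clock** (same section): quality of life is measured "at day 4, 7, 14, 30, 60 and 90 after admission to the hospital; satisfaction with care will be assessed at day 14 after admission".
- **Exposure and size** (sample size paragraph of that section): "We aim to include 100 patients for whom a PCT was consulted and compare them with at least 200 patients receiving usual care". No latest day for the consultation is given.
- **Powered contrast** (same paragraph): a difference on the EORTC QLQ-C15 PAL "at day 14 of 0.4 in standard deviation units", "with alpha of 0.05 (2-sided) and power of 90" per cent.
- **Propensity score** (Data analysis): "We will develop a propensity score model to assess the probability that a patient would have been offered PCT consultation". Matching is on the logit of this score. Days from admission to consultation are neither a covariate nor a matching criterion.
- **Outcome model** (Data analysis): "A model will be fitted that includes matched-pairs, time, treatment group, the baseline score, and interaction between time and treatment group". The baseline score is not defined, and the first listed quality-of-life assessment is on day 4.

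PCTs already complete a questionnaire on the content of the consultation.

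**The concern.** The outcome clock starts at admission, but the exposure starts at some later, variable time. The analysis ignores that gap. A patient first consulted on day 10 brings a day-7 score to the PCT group although no team was yet involved. A patient first consulted after day 14 brings an unexposed day-14 score and an unexposed satisfaction score.

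The day-14 quality-of-life comparison is the one the sample size rests on, and satisfaction is measured only on that day. If the consultation works, unexposed scores in the PCT group shrink the contrast. The quality-of-life change in the cost-effectiveness ratio (Economic evaluation) uses the same instrument, so it inherits the problem unless its exposure is aligned too.

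The listed propensity covariates are patient, physician and hospital characteristics. They do not describe a decline after admission that prompts a consultation, so matching on them does not repair the timing.

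**Working it through.** **1. Which scores are affected.** Let *t* be the day of first consultation, counted from admission. Under the stated rules:

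| First consultation | Scores labelled PCT but taken before it |
|---|---|
| before day 4 | none |
| after day 4, before day 7 | day 4, unless it is the baseline |
| after day 7, before day 14 | day 7 (and day 4, unless baseline) |
| after day 14 | days 7 and 14 and satisfaction (and day 4, unless baseline) |

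The time-by-group term gives each day its own contrast. An unexposed day-7 score therefore does not by itself dilute day 14. The day-14 contrast is affected only by patients with *t* > 14.

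**2. The plan's own figure.** Inputs from the sample size paragraph: 100 PCT, 200 usual care, d = 0.4, two-sided alpha 0.05.

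- Standard error in SD units: √(1/100 + 1/200) = 0.1225.
- Normal approximation: Φ(0.4/0.1225 − 1.96) = Φ(1.306) = 90.4%. The two-sample t-test gives 90.2%.

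The stated 90% is reproduced. It assumes that all 100 PCT patients carry the full effect on day 14.

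**3. Dilution on day 14.** Let *f* be the share of PCT patients first consulted after day 14. The article does not give *f*; the values below are assumptions. If these patients carry no effect on day 14 and the others carry 0.4 SD, the contrast is 0.4 × (1 − *f*). Power is from the t-test with 100 and 200.

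| *f* (assumed) | Contrast (SD) | Power |
|---|---|---|
| 0% | 0.40 | 90.2% |
| 10% | 0.36 | 83.4% |
| 20% | 0.32 | 74.0% |
| 30% | 0.28 | 62.5% |

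**4. Leaving the unexposed patients out instead.** If they do not count as PCT on day 14, the effect stays at 0.4 SD and the group is smaller (t-test).

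| PCT vs usual care | Power at 0.4 SD |
|---|---|
| 80 vs 200 | 85.4% |
| 70 vs 200 | 81.9% |

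At *f* = 20% the aligned contrast has 85% power against 74% for the diluted one. At *f* = 30% it is 82% against 63%. Aligning exposure costs power relative to 90%, but less than dilution does.

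**The case against.** **The time limit is missing, not denied.** The article is condensed and nowhere says that a consultation at any later time counts. It studies in-hospital patients, so consultation during the index stay is a natural reading. That stands as a limit on how many patients are affected. It does not remove the fault: the clock, the group definition and the fixed label are all stated, and consultation within the stay can still follow a day-7 score.

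**The share may be small.** First consultation after day 14 needs a long stay or a counted readmission. The article gives no length of stay and no time to consultation, only an expected stay of at least 3 days. This stands, so the power figures are illustrations.

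**Inferences a reader might draw that the article does not support.**

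- That it admits to frequent late consultation: the discussion says "it is known that PCTs are often consulted relatively late in the disease trajectory". This refers to disease stage, not days since admission; a patient near death may be consulted on the first day.
- That day 4 is always contaminated. If day 4 is the baseline, a score before the consultation is a proper covariate.
- That the estimate would point towards harm. Suppose the late-consulted patients are also 0.3 SD worse than their controls (an assumption). At *f* = 30% the contrast is 0.7 × 0.4 − 0.3 × 0.3 = 0.19 SD, still in favour of PCT. What the figures show is attenuation.

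**The aim is exploratory.** The objectives word it so, and the article concedes possible bias from the observational design. That lowers the severity. It does not cover the timing, because the adjustment offered is for prognostic imbalance.

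**Conclusion.** The point holds. Followed as written, the plan analyses every score taken before a patient's first consultation as a PCT outcome. The scores at risk are day 7, day 4 if it is not the baseline, and, for patients first consulted after day 14, the powered quality-of-life score and the only satisfaction score.

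The size on day 14 depends on a share that the article does not give. At assumed shares of 10%, 20% and 30%, with a true effect of 0.4 SD and none before consultation, the contrast is 0.36, 0.32 and 0.28 SD and power is 83%, 74% and 63%. The 90% calculation is itself correct for its assumption.

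Severity: should fix. The powered comparison is exposed, but the affected share is unknown, the aim is exploratory, and the bias shown is attenuation.

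**What to change.** 1. Record the date of first consultation on the existing PCT questionnaire.
2. Match each PCT patient, at the day of first consultation, to usual-care patients who are alive and not yet consulted at the same number of days since admission. Use the last score before that day as baseline where one exists, and state the rule where none does.
3. Count only assessments after that day as PCT outcomes, and treat earlier scores as unexposed.
4. For the day-14 quality-of-life and satisfaction contrasts, count as PCT only patients first consulted before a pre-specified landmark ahead of day 14. Pre-specify how controls consulted between the landmark and day 14 are handled; otherwise the contamination moves into the control group.
5. Restate the 90% power for the number of PCT patients who qualify.
6. Acknowledge residual confounding by deterioration that prompts the consultation. Neither a landmark nor a plain time-varying exposure term removes it.

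The cost is one date on an existing form, revised wording, and fewer PCT patients in the day-14 contrast. That loss may be more than slight: at 0.4 SD, 80 vs 200 gives 85% power and 70 vs 200 gives 82%. Keeping 100 qualifying PCT patients would mean recruiting more.
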